More than twenty years ago, the question of a higher impact of co-existing SNAP factors on the complication rate than the individual factors alone, was evaluated in a cohort of 26,961 adult patients receiving hernia repair. They exclusively evaluated perioperative respiratory events and found an incidence of 3.1% and a risk rate of 2.4 (95% CI: 1.8-3.2). These outcomes were even higher among overweight smokers below the age of 40 years; 8.0% and a risk rate of 6.3 (4.3-9.2). For comparison, the incidence of respiratory events was only 1.3% among those without smoking and overweight. Another recent cohort study with 55,240 patients evaluated the surgical site infection rate after hernia repair. Here, they found a dose-response with increasing rates at increasing BMI cut-of levels among smokers. BMI (OR 1.04; 95% CI 1.03–1.04;  $p < 0.001$ ) and smoking (1.51; 1.37–1.67;  $p < 0.001$ ) were the two most modifiable risk factors independently associated with this complication. Interestingly, the incidence was only 2% among non-smokers with BMI < 24.2, and 12% for smokers with BMI > 42.3. It would be clinically relevant to evaluate if an 'opposite' dose-response could be identified also during intervention for SNAP factors by the STRONG program. This objective is included in the present STRONG project.

Risky lifestyle plays a further role for recurrence of ventral hernia. A recent systematic review identified smoking (OR 1.34; 1.03-1.74) and BMI above 25 (2.51; 1.37-4.60) as preventable predictors for hernia recurrence as well as complications at the primary repair. Reduction of postoperative complications via successful prehabilitation would further add to the potential for recurrence reduction. However, alcohol and malnutrition were not included in those analyses.

Vi have identified only one study on co-existing SNAP factors performed by Liang and co-workers, who have reported a trend towards less wound complications of an up to six months program with physical exercise + weight reducing intervention: 7% versus 18%,  $p=0.1$ . At 2-year follow-up, there was no effect regarding complication- and recurrence-free patients, 73% versus 66%,  $p=0.4$ .

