### Analyses

Analyses are done blinded as Intention-to-Treat (ITT). We will use Fisher's exact test for frequencies, Mann-Whitney for continuant variables, and  $p < 0.05$  is chosen for statistical significance. To benefit future meta-analyses, we will also give the parametric results. This would also meet the tradition that costs are usually reported with means and standard error (SE), mean difference (MD), and 95% confidence interval (CI). Bootstrapping procedures are used to calculate the cost-effectiveness plane and the acceptability curve by repeatedly resampling the data (1,000 incremental cost and effect pairs). Sensitivity analyses will be performed for differences in local standards for the control groups among the surgical centres. Analyses as per-protocol, dose-response, prediction, sensitivity, and the other secondary analyses are done by logistic regression models including control for confounders and effect-modifiers and reported as Risk Rates with 95% Confidence Interval (CI). The results are considered significant if the CI does not involve 1.00.

Absolute (ARR) is calculated as the events in the control group minus the events in the intervention group, and the relative risk reduction as the ARR divided by the events in the control group. The number needed to treat was calculated by  $1/ARR$ . We will present the mortality as Kaplan-Meier plots and test by the log rank test.

In case of dropouts, the primary outcome is collected from the medical record and a telephone follow-up after acceptance from the patient. In case of missing health data, the lifestyle at baseline will be imputed as the results in order not to over-estimate the results of changing lifestyle. This would expectantly impact the results to a similar degree in both groups.

All quantitative analyses are performed in SPSS Statistics® version 22.

The qualitative analyses are done using Kirsti Malterud's approach of systematic text condensation.

After import into NVivo® qualitative data analysis software version 11, the systematic text condensation in the four steps takes place: 1) Total impression of all answers and identifying preliminary themes, 2) coding by identifying and sorting meaning units, 3) condensation into code groups, and 4) synthesising the condensates into a story grounded in the empirical data.

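### Secondary logistic-regression estimates are to be reported as risk rates with no conversion stated, and the absolute risk reduction is worded without denominators

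*Protocol*

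**What the plan says.** All the relevant text is in the protocol, section 3a, under Analyses.

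- For the main intention-to-treat comparison of proportions: "We will use Fisher's exact test for frequencies".
- The remaining analyses are listed as "Analyses as per-protocol, dose-response, prediction, sensitivity, and the other secondary analyses". Of this whole list the plan then states that they "are done by logistic regression models including control for confounders and effect-modifiers and reported as Risk Rates with 95% Confidence Interval". The decision rule follows: "The results are considered significant if the CI does not involve 1.00". No conversion of the logistic output to the risk scale is described.
- For absolute and relative measures: "Absolute (ARR) is calculated as the events in the control group minus the events in the intervention group", then "the relative risk reduction as the ARR divided by the events in the control group". Finally, "The number needed to treat was calculated by" 1/ARR. None of these sentences gives a denominator.

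Two other places bear on the point. Section 4 states the design effect in rates: complications falling from 20% to 10%. Section 2a (sub-study 5A) plans an analysis of what predicts a repair without complications, which is a common outcome if the design rates hold.

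**The concern.** A logistic model's exponentiated coefficient is an odds ratio. It is close to the risk ratio only when the outcome is rare, and the outcomes here are not rare at the protocol's own figures. An odds ratio printed as a risk rate would be read as a ratio of risks and would appear to show a larger effect.

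What is at stake is the secondary reporting: the per-protocol result, the dose-response and prediction results that answer two of the stated hypotheses, and the sensitivity analyses. The plan also says that it wants to serve later meta-analyses, and an odds ratio pooled as if it were a risk ratio would do the opposite.

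The ARR sentence raises a smaller matter of the same kind. A difference in event counts is not a risk difference, and its reciprocal is not a number needed to treat.

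**Working it through.** **Inputs.** Complication risks of 20% (control) and 10% (intervention), two-sided alpha 0.05, 80% power and 199 per arm come from section 4. Planned size 2 × 200 comes from the Brief Summary. The hernia subgroup of the cited Swedish smoking-cessation trial, 6/21 against 10/17, comes from section 2b.

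**The plan's own figure.** The usual two-proportion formula with pooled variance under the null and no continuity correction gives

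n = [1.960 × √(2 × 0.15 × 0.85) + 0.842 × √(0.2 × 0.8 + 0.1 × 0.9)]² / 0.10² ≈ 199 per arm.

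This matches the stated figure. It rests on the two risks and does not involve the logistic models.

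**Odds ratio against risk ratio.** RR = p₁/p₀ and OR = [p₁/(1 − p₁)] / [p₀/(1 − p₀)], with p₁ for intervention and p₀ for control.

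| Contrast (p₁ vs p₀) | RR | OR |
|---|---|---|
| Complications at the design rates, 10% vs 20% | 0.50 | (0.1/0.9)/(0.2/0.8) = 0.444 |
| Complications at lower rates (assumed), 5% vs 10% | 0.50 | 0.474 |
| Complications at higher rates (assumed), 15% vs 30% | 0.50 | 0.412 |
| Cited hernia subgroup, 6/21 vs 10/17 | 0.486 | (6/15)/(10/7) = 0.280 |
| No complication at the design rates, 90% vs 80% | 1.125 | (0.9/0.1)/(0.8/0.2) = 2.25 |

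Read as a risk ratio, the first odds ratio implies a reduction of 1 − 0.444 = 55.6% instead of 50%. The last row is the complement of the first. The same data that show a 12.5% relative increase in the chance of no complication would carry a risk rate of 2.25.

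**Decision rule.** If p₁ = p₀, both ratios equal 1. The label therefore leaves the comparison with 1.00 essentially unchanged.

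**ARR, RRR and NNT.** With 200 per arm at the design rates there are 40 and 20 events.

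- Literal counts: ARR = 40 − 20 = 20, NNT = 1/20 = 0.05 (impossible), RRR = 20/40 = 50%.
- Proportions: ARR = 0.20 − 0.10 = 0.10, NNT = 1/0.10 = 10, RRR = 0.10/0.20 = 50%.
- Counts with an assumed split of 195 control and 203 intervention: events 39 and 20.3, RRR = (39 − 20.3)/39 = 47.9%.

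Count-based RRR is therefore right with equal arms. With a slightly larger intervention arm it understates the effect.

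**The case against.** The strongest reply is that the protocol names a risk measure as its reporting target, and risk ratios can be obtained from a logistic model. The route from one to the other could sit in a statistical analysis plan that is not shown. That stands to this extent: exaggeration follows only if raw odds ratios are relabelled. It does not rescue the sentence, which pairs this model with that measure and gives no step between them.

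A reader might infer several stronger things that the documents do not support.

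- **That the trial's effect sizes in general would be exaggerated or meaningless.** The logistic sentence does not govern the main comparison, which uses Fisher's exact test. Per-protocol, dose-response and prediction estimates also answer different questions from the intention-to-treat ARR and RRR, so a common scale alone would not make them interchangeable.
- **That the background proves a risk rate here means a risk ratio.** Section 2b relays a cohort that "found an incidence of 3.1% and a risk rate of 2.4 (95% CI: 1.8-3.2", and uses OR for another study. If the quoted 1.3% incidence is the comparator (an assumption), 3.1% gives a risk ratio of 2.38 and an odds ratio of 2.43. Both round to 2.4, so the passage does not settle the meaning.
- **That the quit rates of 51% and 27% in section 2b show the size of the problem.** They give a risk ratio of 1.89 and an odds ratio of 2.81, but they come from an earlier cancer-surgery trial. Between-arm lifestyle frequencies in this trial fall under Fisher's test.
- **That an NNT of 0.05 would be reported.** The ARR sentence has visibly lost words, section 4 works in rates, and an impossible value would be noticed. Loose wording for event rates is the likely reading, and 1/ARR is the standard formula.

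**Conclusion.** The point holds for the secondary analyses fitted by logistic regression. As written, the plan would present odds ratios under a risk label. The distortion is modest for complications at the design rates (0.44 against 0.50) and large for outcomes that most patients have (2.25 against 1.125 for no complication). These figures assume a single two-group contrast without covariates, risks equal to the design rates, and no conversion before reporting. In the prediction analysis the groups compared would be predictor levels and not arms, so the 90% and 80% there are illustrative.

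The primary test, the sample size and the significance decision are essentially untouched. The ARR and RRR wording is a minor correction. It deserves making because the primary outcome is framed as a number of patients while one patient can have several complications, so the term events leaves both numerator and denominator open.

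**What to change.** In section 3a, Analyses:

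1. Label the logistic-regression estimates odds ratios. If a risk measure is intended, say how it is obtained: risk ratios by marginal standardisation from the logistic model, or from a modified Poisson or log-binomial model.
2. Define ARR as the control proportion of patients with the outcome minus the intervention proportion, and RRR as ARR divided by the control proportion. NNT as 1/ARR then needs no change; at the design rates the values are 0.10 and 10.

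This costs a few sentences and changes nothing in design, data collection, sample size or the primary test. Relabelling needs no new analysis. If risk ratios are chosen, the team should confirm that the named software version can produce them, since the protocol does not say.

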## 2. Objectives

### 2a) Problem description, hypotheses, outcomes, and the rationale

Despite the great developments taking place during and after surgery, e.g., intraoperative techniques and enhanced recovery after surgery (the ERAS protocol), there is a large untapped potential for risk reduction in the preoperative period via effective lifestyle intervention targeting one or more co-existing risky lifestyles: Smoking, malNutrition, obesity, risky Alcohol intake and insufficient Physical activity (SNAP).

The STRONG project is national multicentre research with international impact. The overall goal is to obtain the potential extra health gain from the individually tailored, combined and intensive lifestyle intervention – STRONG - in relation to surgery, thereby adding to lower the inequity in health. As SNAP factors are frequent and have a negative social gradient, they strike hardest among disadvantaged patients, thereby developing most postoperative complications. In this project we would be able to reach out to surgical patients, who have not been reachable otherwise.

This clinical research benefits from mixed methods and comprehends several sub-studies:

1. Efficacy of the 6-week preoperative STRONG-program compared to treatment as usual (TAU) on (RCT):
  - A. risky lifestyles, preoperatively and complications, 1-month postoperatively
  - B. risky lifestyles and complications at 3 and 6-month follow-up
2. Efficacy of STRONG compared to TAU on health gain after 6 months and 2-year follow-up
3. Cost-effectiveness of the STRONG program on short and longer term (for 1. A+B and 2.)
4. Prevalence of SNAP factors in the potential study population and the potential for risk reduction.
5. Secondary analyses (Cohort analyses):
  - A. Dose-response of SNAP factor improvement (number/type) and complications as well as predictors for complication-free hernia repair
  - B. Dose-response of SNAP factor improvement (number/type) and health on long-term as well as predictors for improved health
  - C. Associations between self-reported and validated lifestyles
  - D. Associations between patient reflections of motivation, priority, self-efficacy, and lifestyle changes (Nested Qualitative analysis to the intervention group)

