### The hypotheses

The primary hypothesis is that STRONG halves the postoperative complications within 1 month compared to the daily routines.

Secondly, improvement of postoperative complications after 3 and 6 months, risky SNAP lifestyles, health, and the cost-effectiveness as well as improvement of health and costs after 2 years.

In addition, we hypothesise associations

- between preoperative patient reflections and successful change of SNAP factors
- as a dose-response of SNAP factor improvement and complications, as well as predictors for complication-free hernia repair
- as a dose-response of SNAP factor improvement and health gain, as well as predictors for a health gain
- between self-reported and validated SNAP factors.

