### The studies

The project is constituted by several sub-studies all based on data from the RCT with 400 patients as specified in Chapter 2.

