### 4. Statistical considerations: Power calculation

The power calculation is based on the literature as presented above, thus aiming at halving of postoperative complications after intensive programs for smoking, alcohol, and malnutrition. The impact of physical activity is lower, and obesity is sparsely investigated but targeting co-existing SNAP like STRONG should increase the effect due to interactions. Therefore, the main hypothesis is clinically relevant. For ventral hernia in high-risk patients, STRONG would expectantly half the overall complication rate from conservatively 20% to 10%. When using 80% power and 2 x alpha=0.05 we get 2 x 199 participants. This also covers the secondary outcomes regarding lifestyle improvements and costs.

In case of dropping out, the patients are asked to allow follow-up via the medical record system and a telephone interview. It is our experience from previous studies that 90% the drop-out patients accept this. Therefore, the development of complications as the primary outcome will be available for close to all randomised patients. We use block randomisation in rather small groups, which would only to a minimal degree impact the distribution between the intervention and control groups.

In study 4 the prevalence of risky SNAP factors on all patients that potentially could be screened for eligibility in study 1 (about 2 x the included numbers = 800 patients) will be reported as frequencies and 95% CI and analyzed for the potential maximum risk reduction and effects, if they would have received a related STRONG intervention. If possible, the potential will be analyzed for the most frequent combined risk factors.

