## 7. Sampling of blood and urine in our research biobank for biomarkers

All participants have blood and urine tests sampled at baseline and the four scheduled follow-ups for the identification of alcohol- and tobacco biomarkers (B-PetH, U-EtG and U-cotinine), for routine nutrition profile analyses (PI-Protein and PI-Albumin), and routine analyses on B-Hemoglobin, PI-ASAT, PI-Bilirubin as well as for measurement of possible new markers developed during the project period. In total 30 ml blood and 10 ml urine are sampled at each meeting (inclusion and the 4-5 follow-ups with 1-3 months between). Half of the samples is kept for the analyses of new biomarkers possible developed during the project period (see below).

The routine analyses are performed at the local centres. The analyses of the established biomarkers on tobacco and alcohol are performed together for one factor at a time, mainly after collection of all samples. Therefore, it is necessary to collect and store the samples (separated into 1.0 ml in 1.8 ml cryotubes at minus 80° C placed at [name] Bispebjerg-Frederiksberg Hospital) during the project period until analysed. The bio-marker analyses are expected to be performed at the Parker Lab, same address. Left-over samples in the individual tubes used for routine and marker analyses are destroyed immediately afterwards.

As mentioned above, new markers may be developed during the project period, and we would therefore keep half of the samples (i.e., 5x1 ml whole blood and 2x1 ml EDTA plasma, 2x1 ml citrate plasma, 2x1 ml serum, and 5x1 ml urine) stored for further analyses related to measurement of markers for risk reduction at surgery during the study period. Left-over samples will be destroyed after end of the study period (31.12.2033).

In addition, the participants are separately asked about giving informed consent to keep the possible left-over samples stored in a completely anonymised form for future and not yet specified research. It is understood that the samples can be used in future research only after approval from the Scientific Ethical Committee and the Danish Data Protection Agency. If the participants do not give

the separate informed consent, all biological material will be destroyed at the end of the project (as described above)

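### Study 5C's verdict, a ratio whose CI excludes 1.00, shows only that self-report and the validated measure are related, not how well self-report reflects validated lifestyle

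*Protocol*

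**What the plan says.** Protocol section 2a lists study 5C among the secondary (cohort) analyses as "Associations between self-reported and validated lifestyles". The hypotheses in the same section repeat this as an expected association "between self-reported and validated SNAP factors".

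Section 3a, under Analyses, states that "the other secondary analyses are done by logistic regression models including control for confounders and effect-modifiers and reported as Risk Rates" with 95% confidence intervals, and then: "The results are considered significant if the CI does not involve 1.00". 5C is not named there, but it belongs to the group that the sentence covers. The protocol gives 5C no measure of accuracy or agreement.

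The sub-studies are "all based on data from the RCT with 400 patients" (section 3, The studies). Section 7 provides samples from all participants at baseline and follow-up "for the identification of alcohol- and tobacco biomarkers (B-PetH, U-EtG and U-cotinine"). Table 1 schedules self-reported amounts and the biomarkers at the same visits.

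**The concern.** The null hypothesis behind a ratio of 1.00 is that self-report says nothing about the biomarker. That is hardly in doubt, so rejecting it teaches little. What a reader needs from 5C is how often self-report is wrong and in which direction.

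This has a bearing on the trial. Section 2a (The outcomes) makes lifestyle improvement a secondary outcome in both self-reported and validated form. There is also reason to expect under-reporting: the standard protocols in section 3 describe smoking status as unverified by cotinine at all four centres, and at two of them (Horsens and Køge) cessation is mandatory. A result labelled significant could stand beside self-report that misses most users, although the data that would show this are collected.

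**Working it through.** **The plan's own figure.** The only sample-size figure belongs to the primary outcome: "When using 80% power and 2 x alpha=0.05 we get 2 x 199 participants", for 20% against 10%. Check: n = [1.96·√(2·0.15·0.85) + 0.842·√(0.2·0.8 + 0.1·0.9)]² / 0.10² = (0.990 + 0.421)² / 0.01 ≈ 199 per arm. It reproduces. 5C has no sizing of its own and draws on about 400 patients.

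**Inputs for the check.** N = 400 and the decision rule come from the protocol. Prevalence of a positive biomarker, and sensitivity and specificity of self-report, are not given. They are assumptions, shown as ranges.

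**Worked example** (expected 2×2 table, N = 400, prevalence 30%: 120 positive, 280 negative).

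- Poor self-report, sensitivity 40%, specificity 95%: 48 found, 72 missed, 14 false positives, 266 true negatives. OR = (48·266)/(14·72) = 12.7. SE of log OR = √(1/48 + 1/14 + 1/72 + 1/266) = 0.332. 95% CI 6.6 to 24.3. Rule met. RR = (48/62)/(72/338) = 3.6 (2.8 to 4.6). Rule met.
- Good self-report, sensitivity 95%, specificity 98%: 114, 6, 5.6 and 274.4. OR = (114·274.4)/(5.6·6) = 931 (288 to 3006). Rule met.
- Kappa = (observed − chance agreement)/(1 − chance agreement). Poor: (0.785 − 0.638)/(1 − 0.638) = 0.41. Good: (0.971 − 0.580)/(1 − 0.580) = 0.93.
- Sensitivity with Wilson 95% CI: 40% (32% to 49%) against 95% (90% to 98%).

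**How often the rule is met.** Simulated 2×2 tables (at least 20,000 per scenario), 0.5 added to each cell, counting lower Wald 95% limits of the odds ratio above 1.00:

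| N | Sensitivity | Specificity | Prevalence | Rule met |
|---|---|---|---|---|
| 400 | 30–40% | 95–98% | 10–40% | 99.3–100% |
| 400 | 25% | 95% | 15–30% | 99–100% |
| 400 | 25% | 95% | 10% | 97% |
| 400 | 30–40% | 95–98% | 5% | 93–99.8% |
| 400 | 20% | 90% | 5–30% | 36–76% |
| 200 | 25% | 95% | 15–30% | 90–98% |
| 100 | 25% | 95% | 15–30% | 67–79% |
| 100–400 | 90% | 95% | 15–30% | 100% |

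Kappa is about 0.25 at sensitivity 25% and 0.79–0.85 at sensitivity 90% (specificity 95%, prevalence 15–30%). Where both measures were simulated (N = 400), a risk ratio in place of the odds ratio gave the same picture.

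**The case against.** The strongest reply is that the protocol asks about association and the rule tests association. That stands: the method does not contradict the stated hypothesis. A reader might infer that the plan promises to establish self-report as reliable, or that a positive 5C result is meant to validate the self-reported outcomes. The text says neither, and section 3 defines successful risk reduction by validated status.

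Second, estimates and intervals are to be reported, and 12.7 against 931 plainly differ. This also stands, and it confines the point to the significance verdict. Even so, a confounder-adjusted ratio does not give the share or direction of misreporting.

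Third, the models allow for effect-modifiers, so a look by arm is not excluded. True, though arm is not named.

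Fourth, the simulation is unadjusted and its inputs are assumed. This limits the precision of the percentages. It does not alter the logic, since the null remains one of no relation.

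Fifth, a statistical analysis plan might add agreement measures. It might, but the protocol already fixes a method and a decision rule for this group of analyses, and that rule is what is questioned.

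Finally, it is tempting to ask for a between-arm test of under-reporting. For smoking, the documents do not support one. Section 3c offers nicotine replacement in the intervention group, and Table 1 describes the marker as one of nicotine, so a truthful non-smoker on replacement can test positive. Breath CO and the amount of replacement used appear only in Table 4, which is confined to the intervention group. A difference between arms could therefore be an artefact.

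**Conclusion.** The point holds in limited form. The CI-excludes-1.00 verdict answers whether self-report and validated status are related at all. It cannot show how well one reflects the other. Near N = 400, with specificity of 95–98% and prevalence of 10–40%, self-report that finds 25–40% of true positives passes in about 99–100% of trials (97% at sensitivity 25%, specificity 95%, prevalence 10%), and good self-report passes in 100%.

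A reader might infer that the rule is met whatever the quality of self-report. It is not: at sensitivity 20% and specificity 90% it is met in only 36–76% of trials at N = 400, and small subsets also fail more often. Nor is the estimated ratio itself uninformative. The point concerns one secondary analysis and leaves the primary outcome, its sample size and the treatment comparisons untouched.

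**What to change.** In section 3a, take study 5C out of the CI-excludes-1.00 rule and state instead:

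- For each biomarker-validated factor, report unadjusted sensitivity and specificity of self-report, the proportion under-reporting, and kappa, each with a 95% CI, at each visit. State in advance how each measure is classed as positive.
- Base the conclusion on these estimates. Keep the association ratio, or a rank correlation for amounts, as description.
- Show the results by arm descriptively.
- For smoking, draw no between-arm conclusion on under-reporting from cotinine. Use baseline, before the project's nicotine replacement begins, as the main comparison. Within the intervention arm, check later visits against breath CO and recorded replacement use from Table 4.

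The cost is a change of wording and a few extra tables from measurements already scheduled in Tables 1 and 4. The conclusion may turn out less favourable to self-report.
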